**Methods:**

A randomized controlled trial will be conducted among 14–21-year old adolescents with mild to borderline ID and behavioral problems admitted to treatment facilities in the Netherlands. Inclusion criteria are previous substance use and personality risk for substance use. Participants will be individually randomized to the intervention (n = 70) or control (n = 70) groups. The intervention group will be exposed to six individual sessions and five group sessions carried out by two qualified trainers over six-week period. Primary outcomes will be the percentage reduction in substance use (for alcohol: percentage decrease of binge drinking, weekly use and problematic use, for cannabis: the percentage decrease of lifetime cannabis use and weekly use and for hard drug: the percentage decrease of lifetime use). Secondary outcomes will be motives for substance use, intention to use, and internalizing and externalizing behavioral problems. All outcome measures will be assessed after two, six, and twelve months after the intervention.

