### Aims and hypotheses

The main aim of this study is to test the effectiveness of the intervention ‘Take it personal!’ in decreasing substance use among adolescents (age 14 – 21 years old) with mild to borderline ID and behavioral problems who are admitted to treatment facilities in the Netherlands. The effectiveness of the intervention is being assessed by conducting a randomized controlled trail (RCT) with two conditions (treatment and control group). Follow-up assessments will be carried out at two, six, and twelve months after the start of the intervention.

The main hypothesis is that the intervention will reduce alcohol, cannabis, and hard drug use among individuals in the intervention group compared to those in the no-intervention control group. We also expect a decrease in the intention to use alcohol, cannabis and/or hard drugs in the future, a change in motives for alcohol and/or drug use after two, six, and twelfth moths in the intervention group compared with the control group. In addition, the effect of the program on internalizing and externalizing behavioral problems will be tested after two, six and twelve months after start of the intervention. We hypothesized that the intervention would decrease internalizing and externalizing behavioral problems in the intervention group compared with the control group.

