After selecting the treatment centers, adolescents will complete a screening questionnaire to identify adolescents who meet the inclusionary criteria. Adolescents will be eligible to enter the trial if they meet the following inclusion criteria: (1) life time prevalence of alcohol, cannabis, or hard drug use, (2) belonging to one of the four personality high-risk groups (SS, IMP, AS or NT), and (3) providing signed informed consent along with the signed informed consent from parents or legal representative. Adolescents scoring more than one standard deviation above the sample mean on one of the four high-risk personality scales of the Substance Use Risk Profile Scale (SURPS) [40] will be classified as belonging to that risk profile. Adolescents who will score above the average on more than one personality profile will be assigned to the profile for which they showed the largest statistical deviation with respect to the z-score (cf. [17]). Adolescents with addiction problems will be excluded from participation in the intervention and the trial because this intervention is not considered sufficient for them. For these adolescents, treatment will be organized in collaboration with a regional institute for addiction care. Parents or legal representatives will be informed about the study through a letter sent home, asking them to contact the researchers by phone or email if they do not wish their child to participate in the screening (passive informed consent). Adolescents will be informed on the day of the screening, at which time they have the option not to participate in the trial. Parents (when participants are under the age of 18 years) and adolescents will need to provide active informed consent to participate in the RCT. After the screening questionnaire and informed consent, the adolescents will be individually randomized to either control condition or experimental condition.

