### Outcomes

‘Take it Personal!’ aims to decrease substance use among adolescents with mild and borderline ID. We operationalized goals for limiting alcohol, cannabis, and hard drug use. The primary outcome of alcohol use will be the percentage of decrease in binge drinking, weekly use, and problematic use. The primary outcomes of cannabis use will be the percentage of decrease in lifetime cannabis use and weekly use. The primary outcome of hard drug use will be the percentage of decrease in lifetime use. These outcome measures will be assessed at baseline and two, six, and twelfth months after the intervention using the Substance Use and Misuse among Intellectually Disabled Persons Questionnaire (SumID-Q; [43]). This questionnaire is specifically developed to measure substance use among people with intellectual disabilities. Secondary outcomes are the intention to use less alcohol and/or drugs in the future [44, 31], motives for alcohol and/or drug use (Drinking Motives Questionnaire-Revised-Short Form (DMQ-R-SF) [45], and internalizing and externalizing behavioural problems measured by YSR [46]. Adolescents with mild to borderline ID are able to complete self-report instruments with some support [47]. Therefore, all measures will be supported using structured interviews.

This study examined the effectiveness of ‘Take it Personal!’ in daily practice (effectiveness trial). In this case, it is important to monitor the program fidelity [48, 49]. For this reason, we will monitor five domains: 1) adherence, 2) exposure (dosage), 3) quality of the delivery, 4) responsiveness of the participant, and 5) program differentiation (cf. [49]).

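### Two of the six primary outcomes are a decrease in lifetime use, which cannot occur within a person, so reduction in hard-drug use has no usable primary outcome

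*Protocol article*

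**What the plan says.** The Outcomes section of the protocol article lists the primary outcomes by substance, each as a percentage decrease.

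- Alcohol (three): "The primary outcome of alcohol use will be the percentage of decrease in binge drinking, weekly use, and problematic use".
- Cannabis (two): "The primary outcomes of cannabis use will be the percentage of decrease in lifetime cannabis use and weekly use".
- Hard drugs (one): "The primary outcome of hard drug use will be the percentage of decrease in lifetime use".

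On timing, the section says: "These outcome measures will be assessed at baseline and two, six, and twelfth months after the intervention". The Methods paragraph of the abstract repeats both lifetime outcomes, for example "for hard drug: the percentage decrease of lifetime use".

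Aims and hypotheses gives the main hypothesis as follows: "the intervention will reduce alcohol, cannabis, and hard drug use among individuals in the intervention group compared to those in the no-intervention control group". The Discussion paragraph of the abstract and the opening of the main Discussion also expect a reduction.

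The first inclusion criterion, under Recruitment, is "1) life time prevalence of alcohol, cannabis, or hard drug use". Use of any one of the three classes is enough. The Statistical analysis section compares the intervention arm with the control arm, by intention to treat with multiple imputation and again in completers.

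**The concern.** Lifetime use moves in one direction only: a person can go from never to ever, but not back. An outcome defined as a decrease in lifetime use therefore names a change that cannot take place in any participant. The programme is aimed at adolescents who have already started using substances, and the hypothesis is that they will use less. On these two outcomes, a cannabis or hard-drug user who stops completely looks the same as one who carries on unchanged.

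For cannabis this spoils one of two primary measures. For hard drugs it spoils the only one, so the trial could end with no primary evidence either way on a third of its main hypothesis. If a decrease did appear in the data, it could be misread as benefit.

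**Working it through.** **1. Count of outcomes.** Alcohol 3 + cannabis 2 + hard drugs 1 = 6. Lifetime use accounts for 1 of 2 for cannabis and 1 of 1 for hard drugs, so 2 of 6.

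**2. Is lifetime use meant literally?** Three readings of the text say yes. Lifetime and weekly cannabis use are listed side by side as different measures. The inclusion criterion uses the term in its ordinary sense of ever having used. No recall window redefines it, and the abstract and the Outcomes section agree.

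**3. Direction of change.** Let L(t) be 1 if a participant has ever used by time t, and 0 otherwise. L(t) cannot fall over time, so the decrease L(0) - L(t) is 0 or -1 for everyone. In a fixed cohort the largest true decrease in prevalence is 0 in either arm. A within-person decrease in the data must be inconsistent self-report. Apart from that, a group-level decrease could come only from dropout or imputation.

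**4. What the outcome can still detect.** With baseline lifetime use b and onset c among never-users, follow-up lifetime prevalence is b + (1 - b)c. The arms can differ truly through c, and only through c.

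**5. The plan's own sample size.** Inputs from Power analyses: f = 0.25 (d = 0.50 for two groups), two-sided alpha 0.05, power 0.80, 10% loss. Per arm, n = 2(1.960 + 0.842)²/0.50² = 62.8, so 63. The total is 126, and 126/0.90 = 140, as stated. The figure reproduces and is not affected by this point. It leaves 63 evaluable per arm.

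**6. Power to detect fewer new starts.** Assumptions, not given by the plan:

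- Baseline lifetime use is 25% or 50%. This range is borrowed from the Background figure for occasional or regular drug use, mainly cannabis. The documents give no hard-drug figure.
- Control onset over 12 months is 10%, 20% or 30% of never-users.
- The intervention halves onset.
- No allowance is made for clustering by centre.

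Formula, with p̄ the mean of the two proportions:

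power = Φ{ [|p1 - p2| - 1.96 √(2p̄(1 - p̄)/n)] / √([p1(1 - p1) + p2(1 - p2)]/n) }

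Worked case: b = 25%, so never-users per arm = 63 × 0.75 = 47.25. With onset 30% v 15%, p̄ = 0.225, and the two standard errors are 0.0859 and 0.0845. Power = Φ[(0.15 - 1.96 × 0.0859)/0.0845] = Φ(-0.22) = 0.41.

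| Baseline lifetime use | Never-users per arm | Onset, control v intervention | Power, never-users | Follow-up prevalence, control v intervention | Power, all 63 per arm |
|---|---|---|---|---|---|
| 25% | 47 | 10% v 5% | 0.15 | 32.5% v 28.75% | 0.07 |
| 25% | 47 | 20% v 10% | 0.27 | 40% v 32.5% | 0.14 |
| 25% | 47 | 30% v 15% | 0.41 | 47.5% v 36.25% | 0.25 |
| 50% | 32 | 10% v 5% | 0.11 | 55% v 52.5% | 0.05 |
| 50% | 32 | 20% v 10% | 0.20 | 60% v 55% | 0.08 |
| 50% | 32 | 30% v 15% | 0.29 | 65% v 57.5% | 0.14 |

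Power is 0.11-0.41 among never-users and 0.05-0.25 using everyone. If the intervention abolished onset altogether, the same grid would give 0.44-0.99 and 0.08-0.75. The weakness therefore depends on the assumed effect.

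**The case against.** The strongest reply is that the analysis compares arms and does not test change within a person. An adolescent who has only drunk alcohol is eligible and may start cannabis or hard drugs during the year. Lifetime use can then differ truly between arms, and fewer new starts is a sensible aim for a programme described as preventive. This stands, and it limits the point in several ways.

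- A reader might infer that the two outcomes cannot be tested or have no power. That goes too far. They can be compared between arms as a measure of onset, and power is low rather than nil under the assumptions above.
- A reader might infer that the true change is zero in both arms. The argument bounds only its sign: lifetime use stays level or rises, and the rise can differ by arm.
- A reader might infer that half of the cannabis hypothesis is lost. It is not. Weekly cannabis use is also primary, is reversible, and tests the reduction.
- A reader might infer that most participants are already ever-users of the drug in question. The documents do not show this. Entry can be met through alcohol alone, adolescents with addiction problems are excluded, and there is no hard-drug figure.
- A reader might infer that changed reporting would favour the intervention arm. The protocol acknowledges possible error in self-report but gives nothing on its size or direction by arm.

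The reply does not rescue the outcomes as written. Prevented onset is neither the decrease named in the Outcomes section nor the reduction hypothesised, and it says nothing about existing users.

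**Conclusion.** The point holds in this form: a decrease in lifetime use is wrong as a primary outcome for cannabis and for hard drugs, because reduction or cessation among existing users cannot register on it. This affects two of six primary outcomes. The serious consequence is for hard drugs, where no other primary outcome exists and the hypothesised reduction cannot be shown.

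The argument about direction needs no assumption beyond the ordinary meaning of lifetime use. The statement that the remaining onset comparison would probably be weak (power about 0.05-0.41) rests on the assumed baseline use, onset rates and halving of onset. It is not a claim that the comparison is impossible.

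This is not a detail left to a fuller document. The article states these outcomes outright, twice.

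**What to change.** In the abstract (Methods) and the Outcomes section, replace lifetime cannabis use and lifetime hard-drug use with any use in a defined recent period, yes or no. The period could be the past month or the time since the previous assessment, provided the baseline question covers a comparable window. Ask it at baseline and at each follow-up in the same structured interview. The primary outcomes then match the reduction stated under Aims and hypotheses.

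If a lifetime item is kept, define it as onset among participants who had never used that substance at baseline, and label it secondary.

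Cost: a registry update, and possibly one added question per substance. The content of the substance-use questionnaire is not shown, so it may already hold a recent-use item. No change to the 140 participants follows from this point. Recent hard-drug use may be uncommon, particularly as adolescents with addiction problems are excluded, so that estimate may be imprecise and should be reported with its confidence interval.

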### Statistical analysis

Descriptive analyses will be conducted to examine whether the randomization results in a similar distribution of demographic factors and outcome measures in both conditions. Variables that show different distributions between the two groups will be entered as confounders in all models testing the effectiveness of the intervention. The effect of the intervention program on the primary and secondary outcome variables will be tested in accordance with the intention-to-treat principle and in a completers-only framework by using Mplus [50]. Intention-to-treat means that all participants will be analyzed in the condition to which they will be assigned by randomization. Missing data will be handled by multiple imputation (MI). A total of 20 datasets will be completed by multiple imputation. Mplus will read the 20 datasets via the TYPE = IMPUTATION option and will carry out the desired analyses for each dataset. Mediating the parameter estimates will then aggregate the results for the 20 analyses. With respect to the completers-only analyses, only the participants with scores for all time points will be included. In both the intention-to-treat and the completers-only analyses, the effect of the intervention condition will be compared to the control condition. Because the data have a multilevel structure (i.e., individuals are ‘clustered’ within treatment centres), the individual respondents within treatment centres may be interdependent. To correct for the potential non-independence (complexity) of the data, the TYPE = COMPLEX procedure in Mplus will be used. This procedure corrects the standard errors of the parameter estimates for dependency, leading to unbiased estimates. The results of the study will be reported in accordance with the CONSORT statement [51, 52].

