### Power analyses

In the present study, we aimed to show a medium effect size (cf. [14]). Power-analysis was conducted based on an average effect size of f = 0.25 [41], a 2-sided test at alpha = .05, a statistical power (1-beta) of 0.80, and 10 % loss-to-follow-up after randomization. Based on these assumptions a sample size of 140 adolescents (70 in each condition; G-power) is required. Eighteen intervention groups are required, assuming that up to a maximum of four participants will be included in intervention group.

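### Covariates enter the effect models only when the arms differ at baseline; the baseline outcome should be adjusted for whatever the observed balance

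*Protocol article*

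**What the plan says.** The Statistical analysis section of the protocol article begins with a baseline comparison: "Descriptive analyses will be conducted to examine whether the randomization results in a similar distribution of demographic factors and outcome measures in both conditions". The next sentence turns that comparison into a modelling rule: "Variables that show different distributions between the two groups will be entered as confounders in all models testing the effectiveness of the intervention". The rule covers every effect model, and the variables screened include the outcome measures themselves.

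Three other statements bear on it:
- Allocation (abstract, Methods): "Participants will be individually randomized to the intervention (n = 70) or control (n = 70) groups".
- Availability of baseline values (Outcomes): "These outcome measures will be assessed at baseline and two, six, and twelfth months after the intervention".
- Form of the outcome (Outcomes): for alcohol, "The primary outcome of alcohol use will be the percentage of decrease in binge drinking, weekly use, and problematic use", with similar wording for cannabis and hard drugs.

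The article gives no criterion for when two distributions count as different. It does not set out the effect model, and no sentence says that the baseline outcome is always included.

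**The concern.** A confounder must be related to both treatment and outcome. Individual randomisation removes any systematic relation to treatment, so what makes a covariate worth including is how well it predicts the outcome. The rule selects on the other property, chance imbalance. Three things follow:

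- A variable with no bearing on outcome can enter every model because it happens to differ.
- The baseline value of the outcome, usually the best predictor available, enters under this sentence only if it looks imbalanced.
- The final model is known only after baseline data are inspected, and its standard errors take no account of that step.

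At stake are precision in a trial of 140 and a clearly prespecified primary model. Protection against false positives is not at stake if the rule is applied as written.

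**Working it through.** **Inputs from the article (Power analyses).** "Power-analysis was conducted based on an average effect size of f = 0.25", "a 2-sided test at alpha = .05", power 0.80, 10% loss to follow-up, 140 randomised.

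**Inputs assumed, because the article does not give them.** Baseline-to-follow-up correlation ρ of 0.3 / 0.5 / 0.7; imbalance declared at p < 0.05 (p < 0.20 as a variant); no baseline term unless flagged; a continuous follow-up score in the main calculation.

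**Step 1: reproduce the stated sample size.** For two equal groups d = 2f = 2 × 0.25 = 0.5. Then n per arm = 2 × (1.960 + 0.842)² / 0.5² = 62.8, rounded up to 63, or 126 in total. Allowing for loss, 126 / 0.90 = 140, as stated. The checks below use 63 evaluable per arm.

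**Step 2: what constant adjustment buys.** Adjusting for baseline multiplies the residual variance by 1 − ρ². Power is approximately Φ(0.5 / √(2(1 − ρ²)/63) − 1.96):
- ρ = 0.3: Φ(2.94 − 1.96) = 84%
- ρ = 0.5: Φ(3.24 − 1.96) = 90%
- ρ = 0.7: Φ(3.93 − 1.96) = 98%

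The n per arm for 80% power, 62.8 × (1 − ρ²) rounded up, would be 58 / 48 / 33 instead of 63.

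**Step 3: simulate the rule.** Each simulated trial compares the baseline outcome between arms. If p < 0.05 it uses ANCOVA, otherwise the unadjusted comparison.

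| ρ (assumed) | Type I error, rule | Power, rule | Power, always adjusted |
|---|---|---|---|
| 0.3 | 4.8% | 80% | 83% |
| 0.5 | 4.2% | 80% | 89% |
| 0.7 | 3.7% | 82% | 97% |

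A separate run with 60,000 null and 20,000 alternative trials per setting agrees to within about one percentage point: type I error 4.8% / 4.3% / 3.6%, power 80% / 81% / 82% against 83% / 90% / 97%. Type I error with constant adjustment was about 5% throughout.

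The direction has a simple explanation. When baseline is not flagged, the arms are known to be fairly close on a prognostic variable, so the unadjusted difference varies less than its standard error claims.

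**Step 4: vary the assumptions.**
- *Looser screen, p < 0.20.* Type I error 4.6% / 3.7% / 2.7% and power 80% / 83% / 86% at ρ = 0.3 / 0.5 / 0.7. The rule becomes more conservative and recovers part of the power.
- *Yes/no outcome*, logistic model, assumed 40% against 19%, latent correlation 0.5 / 0.8, 4,000 runs per setting. Power 73% / 75% under the rule against 78% / 88% always adjusted, a gain of 5 to 13 points. Type I error 4.5% / 4.2%.
- *Change from baseline*, with ANCOVA only if flagged at p < 0.05. Power 66% / 81% / 95% against 83% / 90% / 97% at ρ = 0.3 / 0.5 / 0.7, a gain of 17 / 9 / 2 points. Type I error 3.9% to 4.4%.

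**Step 5: how often chance changes the model.** With k independent variables screened at 0.05, the chance of at least one flag is 1 − 0.95^k: 26% for k = 6, 40% for k = 10, 54% for k = 15. The primary outcomes alone supply six measures (three alcohol, two cannabis, one hard drug). Independence is a simplification, since these measures are likely to be correlated.

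**The case against.** The strongest reply is that the article states only which extra variables are added. It does not give the underlying model, so the baseline outcome may be there already, either as a standing term or because the outcome is a decrease from baseline. Model form is commonly left to an analysis plan that is not at hand. This stands: the power figures are conditional, and a reader should not infer that the baseline outcome is definitely left out. What remains is that outcome measures are among the variables the rule screens, so the text treats their inclusion as contingent on imbalance.

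The main figures also use a continuous score, while the primary outcomes are largely yes/no measures such as weekly or lifetime use. That too stands, and is why the other variants are reported.

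Other stronger readings are tempting but unsupported:
- *The rule inflates type I error.* Applied as written it does the reverse, modestly. Choosing covariates after seeing results could behave differently, but nothing in the article says that this is intended.
- *The plan uses baseline significance tests.* It speaks of descriptive analyses and names no test. The 0.05 screen is an assumption made here.
- *The sample size is wrong.* It reproduces exactly and does not depend on this point.
- *Centre, personality profile, age and sex should go into every model.* With about ten centres (Recruitment), that is 1 intercept + 1 treatment + 1 baseline + 9 centre + 3 profile + 1 age + 1 sex = 17 parameters for 126 evaluable participants. A null logistic simulation of such a model gave type I error of 6–7% at assumed prevalences of 40% and 20%. Separation occurred in about 6% / 57% / 97% of fits at 40% / 20% / 10%. Centre is already handled by the Mplus TYPE = COMPLEX correction, and the article does not name sex as a collected variable.

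**Conclusion.** The concern holds in a limited form. The article fixes a covariate rule for all effect models on a criterion that randomisation makes uninformative. The consequence is a model that depends on chance imbalance and probably some lost precision. It is a weakness worth correcting and does not invalidate the trial.

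As to size, type I error falls slightly below 5% in every setting examined. The power forgone, if baseline is otherwise absent and the outcome is continuous, is about 3 points at a correlation of 0.3, 9 at 0.5 and 15 at 0.7. The range across the other outcome types examined at the p < 0.05 screen is about 2 to 17 points. All of this rests on assumed correlations, an assumed screening threshold and an assumed model. That the rule selects covariates on the wrong property depends on none of these.

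**What to change.** Replace the sentence on confounders with text along these lines: *Every effect model adjusts for the baseline value of the same outcome, whatever the observed balance; any further covariates are a short list fixed before data are seen. Baseline comparability is reported descriptively and does not change the model; adjustment for imbalanced variables is a labelled sensitivity analysis.*

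Keep centre in the existing TYPE = COMPLEX correction. Do not add some ten centre terms, personality profile, age and sex to every model, because sparse yes/no outcomes cannot support them.

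The cost is a short text change. The baseline outcomes are already to be measured, so no participants or visits are added. The one drawback concerns outcomes on which hardly anyone changes status, such as lifetime use: there the baseline term may need a simpler form, which should also be settled in advance.

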## Participants

### Recruitment

‘Take it personal!’ was developed for adolescents (14–21 years) with mild to borderline ID who are admitted to treatment centers in the Netherlands. These adolescents often have severe internalizing (anxiety, depression) and externalizing (aggression, antisocial behavior) behavioral problems or psychiatric diagnoses. Participants will be recruited through treatment centers. About ten treatment centers in the Netherlands will be invited to participate in this RCT. These treatment centers offer specialized residential and extramural care for adolescents with mild to borderline ID and severe behavioral problems. A team of therapists will implement the intervention and behavioral scientists and participating institutions will receive the materials for ‘Take it personal!’ free of charge.

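### With about ten centres, the planned centre-clustered standard errors are too small on average, and a nominal 5% test rejects in about 8–12% of null trials if a normal reference is used

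*Protocol article*

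**What the plan says.** The Statistical analysis section of the protocol article treats participants as clustered in treatment centres and names TYPE = COMPLEX in Mplus as the remedy, for primary and secondary outcomes. It then states a property without qualification: "This procedure corrects the standard errors of the parameter estimates for dependency, leading to unbiased estimates".

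Three other statements bear on it:

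- Recruitment, on the number of clusters: "About ten treatment centers in the Netherlands will be invited to participate in this RCT". This is the number approached; the number taking part may be lower.
- Recruitment, on allocation: "the adolescents will be individually randomized to either control condition or experimental condition". Both arms can therefore occur within a centre.
- Power analyses, on the nominal error: "a 2-sided test at alpha = .05".

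The article mentions no adjustment for a small number of clusters. It does not say which reference distribution or finite-sample factor will be used.

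**The concern.** A cluster-robust (sandwich) variance is justified as the number of clusters grows. With few clusters two things go wrong. The estimated standard error is on average below the true sampling standard deviation, and it varies a good deal from one trial to the next. A normal critical value of 1.96 allows for neither.

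The procedure is applied throughout. The Outcomes section lists six primary substance-use measures (three for alcohol, two for cannabis, one for hard drugs) at three follow-ups, so 6 × 3 = 18 primary comparisons, before the secondary outcomes. If each runs above its nominal level, a claim of effectiveness rests on weaker evidence than its p-value suggests.

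**Working it through.** **Step 1. Reproduce the plan's sample size.** Inputs from Power analyses: "Power-analysis was conducted based on an average effect size of f = 0.25", "a 2-sided test at alpha = .05", "a statistical power (1-beta) of 0.80", "10 % loss-to-follow-up after randomization". For two groups d = 2f = 0.50.

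- n per arm = 2(1.960 + 0.842)² / 0.50² = 62.8, rounded up to 63; total 126.
- Allowing for loss: 126 / 0.90 = 140, the stated figure.

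The checks below use 126 analysed participants, with 140 as a variant.

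**Step 2. Analytic approximation.** With k centres, treat the robust statistic as t with k − 1 degrees of freedom but compare it with 1.96. If the variance lacks the factor k/(k − 1), the effective cut-off falls to 1.96 × √((k − 1)/k); for k = 10 this is 1.96 × √0.9 = 1.859.

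| Centres | With factor: P(\|t\| > 1.96) | Without factor |
|---|---|---|
| 6 | 10.7% | 13.4% |
| 8 | 9.1% | 10.9% |
| 10 | 8.2% | 9.6% |
| 12 | 7.6% | 8.7% |
| 20 | 6.5% | 7.1% |
| 40 | 5.7% | 6.0% |

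**Step 3. Simulation under no treatment effect.** Individual 1:1 randomisation, a linear model, and a sandwich clustered on centre; 5,000–10,000 runs per setting. The centre ICC (0, 0.05 or 0.15) and the centre sizes (equal or unequal) are assumed, as the article gives neither.

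| Ten centres | With factor | Without factor |
|---|---|---|
| Rejection, continuous outcome, normal reference | 7.8–9.7% | 9.4–11.2% |
| Rejection, binary outcome, unequal centres, normal reference | 9.5–10.2% | 11.0–11.8% |
| Mean standard error / true standard deviation | 0.93–0.97 | 0.88–0.92 |

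The last row is the source of the 3–12% shortfall: 1 − 0.97 = 0.03 and 1 − 0.88 = 0.12. The assumed ICC made little difference; the number of clusters and the normal reference drive the result. With eight centres (continuous outcome), rejection was 9.1–11.0% with the factor and 10.8–13.2% without. A separate simulation, with zero to four covariates and a group ICC of 0–0.10, gave 8.8–12.3% for ten centres.

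**Step 4. Does dependence within intervention groups change this?** 126 participants, ten unequal centres, centre ICC 0.05, factor applied, 6,000 runs.

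| Group ICC | Normal reference | t, 9 df |
|---|---|---|
| 0 | 9.0% | 5.7% |
| 0.05 | 8.8% | 5.9% |
| 0.10 | 8.7% | 5.3% |

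Rejection does not rise with the group ICC.

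**Step 5. Change only the reference.** In the Step 3 settings with ten centres, the same standard error (with factor) referred to t on 9 df rejects in 4.7–6.7% of null trials, mostly between 5% and 6.5%.

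**The case against.** Several points on the other side are sound and limit what can be concluded.

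- **Undocumented details.** The article gives neither the reference distribution nor the finite-sample factor, and a condensed article may leave these to a fuller plan. If a small-sample t reference were used, most of the problem would go. This stands, which is why the size is a range tied to an assumption. It does not rescue the unqualified statement, made where about ten clusters are foreseen.
- **What is unbiased.** The sentence can be read as being about the treatment effect itself. A reader might infer that the effect estimate is biased; it is not, because allocation is randomised. The defect lies in the standard error and the test.
- **Intervention groups.** The power section says "Eighteen intervention groups are required", and a reader might infer that dependence within those groups goes unhandled. The Intervention section places the group sessions at the participant's own institution, so groups are nested in centres. A centre-level sandwich allows for any dependence inside a centre, and Step 4 agrees.
- **Not every interval.** A reader might infer that every confidence interval will be too narrow. The shortfall is an average: in one check the standard error exceeded the true value in about 40% of runs. Much of the excess rejection comes from this variability combined with a fixed 1.96.

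One could also argue for ignoring centre, since individual randomisation largely removes centre effects from the comparison; that test rejected in 4.6–5.9% of the Step 3 null trials with ten centres. Those runs had no group dependence, however. At a group ICC of 0.10 a test ignoring centre rose to 6.2–6.9%, so keeping the clustering with a proper reference is reasonable.

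**Conclusion.** The concern holds for the standard errors and tests, not for the point estimate. With ten centres the standard errors are on average 3–12% too small, and a nominal 5% test runs at about 8–12% under a normal reference; fewer participating centres would make it worse. The claim that the procedure leads to unbiased estimates should not stand unqualified at this number of clusters.

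The size rests on assumptions the article does not settle: a normal reference, the finite-sample factor (both cases shown), the ICCs, the spread of centre sizes, and a linear model for binary outcomes. The simulations do not include the planned imputation of 20 datasets. None of this calls for a change to design or recruitment.

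**What to change.** Keep clustering on treatment centre. Specify a small-sample bias-corrected cluster variance and refer the statistic to t with (number of participating centres − 1) degrees of freedom. Replace the sentence on unbiasedness with one saying that the correction is approximate when clusters are few. The 5–6.5% error was obtained with the simple k/(k − 1) factor and the t reference; fuller bias corrections were not simulated here.

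The cost is a change of wording, possibly other software for the corrected variance, and wider intervals with some loss of power. For ten centres the critical value rises from 1.960 to 2.262, and 2.262 / 1.960 = 1.154, so intervals widen by about 15%. If the factor is not already applied, √(10/9) = 1.054 and 1.154 × 1.054 = 1.216, about 22% in all.

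A model with centre as a fixed effect and a random effect for intervention group, in the intervention arm only, may serve as a sensitivity analysis where the outcome allows it. It is less suitable as the main analysis: the primary outcomes are largely use or non-use, and with 126 / 10 ≈ 13 participants per centre some centres may show no variation, so that their fixed effects cannot be estimated in a logistic model.
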